**Fig 2 pone.0280856.g002:**
[figure not shown]
The SPIRIT schedule for the study.

**Fig 3 pone.0280856.g003:**
[figure not shown]
Flow diagram for the study.

### Variables

#### Primary outcome variables

The participants’ oral health status will be the primary outcome variable. There would be three measures, including the caries experience, which would be based on the oral examination of the dmft/DMFT scores, current caries status [48], and oral hygiene status [47].

The DMFT/dmft will be calculated for each participant by summing up all the carious, filled, and missing teeth due to caries in their mouth. Subsequently, the mean DMFT and mean dmft will be calculated by dividing the sum of the DMFT/dmft scores for each group by the total number of participants in the group and reported separately for the two study groups. The caries prevalence would also be assessed by dividing the number of participants with at least one carious tooth over the total number of participants in each group.

The oral hygiene status will be assessed using the simplified Oral Hygiene Index (OHI-S) [47]. The maximum score for OHI-S is six. Based on their score, each participant will be assigned these three categories: “Good” (0.0–1.2), “Fair” (1.3–3.0), and “Poor” (3.1–6.0) [47].

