### Sample size determination

The sample size for this study was determined using the formula for comparing two proportions [41]. The primary outcome is oral hygiene status. The prevalence (P_1_ = 38.4%) of children who had good oral hygiene from a previous study in Nigeria [42], was used for sample size calculation. An estimated 50% increase in the proportion of participants with good oral hygiene following the intervention (P_2_ = 57.6%) was used in calculating the minimum sample size. Other considerations were statistical power of 80%, a significance level of 5%, a non-response rate of 10%, an attrition rate of 20%, and an estimated design effect of 1.5. A minimum of 212 participants will be recruited per study group, making 424 for the two groups.

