#### Data analysis plan

Baseline data would be compared among the two study groups based on their sociodemographic characteristics and the baseline value of the outcome variables (oral hygiene status, DMFT/dmft, caries status, knowledge, attitude, and practice). Subsequently, the intervention effects on the outcome variables will be assessed over the study period (baseline, immediate, 6 months, and 12 months assessments). The effectiveness would also be compared between groups (test vs control) over the 12 months (baseline, 6 months, and 12-month assessment). An intention-to-treat analysis will be employed for this study [51]. A participant will remain in the originally assigned group, notwithstanding what happens during the study, such as deviation from the study protocol or loss to follow-up. The data obtained at the previous assessment will be recorded for those lost to follow up in the subsequent assessments. The level of statistical significance for all tests will be set at p < 0.05.

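### The sample size section names one primary outcome, oral hygiene status; the outcome section makes three measures primary, two of them with no power basis and none ranked

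*Protocol article*

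**What the plan says.** Four sections of the protocol article bear on this point.

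- **Sample size determination:** "The primary outcome is oral hygiene status". The two proportions are 38.4% ("The prevalence (P_1_ = 38.4%) of children who had good oral hygiene from a previous study in Nigeria") and 57.6% ("good oral hygiene following the intervention (P_2_ = 57.6%) was used in calculating the minimum sample size"). The allowances, in which the design effect is 1.5, are listed as "statistical power of 80%, a significance level of 5%, a non-response rate of 10%, an attrition rate of 20%, and an estimated design effect of" that size. The result: "A minimum of 212 participants will be recruited per study group, making 424 for the two groups".
- **Primary outcome variables:** "oral health status will be the primary outcome variable. There would be three measures, including the caries experience". The other two measures are current caries status and oral hygiene status by OHI-S. OHI-S is cut into three categories, with Good defined as 0.0 to 1.2.
- **Secondary outcome variables:** only knowledge, attitude and practices are listed. The caries measures are therefore not placed among the secondary outcomes.
- **Data analysis plan:** "The level of statistical significance for all tests will be set at p < 0.05". Between-group effectiveness is compared across baseline, 6 and 12 months.

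The Discussion adds that the study should yield evidence on each outcome on its own.

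**The concern.** The primary outcome decides whether the trial is read as positive. Here one section gives that role to oral hygiene status alone, and another shares it among three measures. The sections overlap but give different answers to a simple question: would a significant difference in caries, with no difference in oral hygiene, be a primary result? Under the sample size section it would not. Under the outcome section it could be.

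Two things are at stake. First, the stated 80% power belongs to one of the three measures; the document gives no caries rate, standard deviation or target effect, so power for the other two cannot be worked out. Second, every test is set at the 5% level with no ranking, alpha split or all-must-succeed rule, so the error rate of the primary claim is not fixed.

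**Working it through.** **1. Which outcome does the sample size cover?**

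Inputs from the sample size section: P1 = 0.384, P2 = 0.576, difference 0.192, mean 0.48, power 80%, alpha 5%. Two-sided testing is assumed, since the sidedness is not stated.

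Pooled two-proportion formula:

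n = [z(1−α/2)·√(2·0.48·0.52) + z(0.80)·√(0.384·0.616 + 0.576·0.424)]² / 0.192²

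= [1.960·0.7065 + 0.8416·0.6934]² / 0.036864 = 105.1, rounded up to 106 per group.

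Inflation: 106 × 1.5 (design effect) = 159; 159 / 0.9 (non-response) = 176.7; 176.7 × 1.2 (attrition) = 212.0. This is the plan's figure exactly, with no caries input. The order and form of the loss allowances are inferred. Dividing by 0.9 × 0.8 instead gives 159 / 0.72 = 220.8, which does not match.

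**2. Error rate if any one of the three measures could support the claim**

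Three tests, each two-sided at 5%. Independent: 1 − 0.95³ = 0.143. Upper bound: 3 × 0.05 = 0.15. With correlation, by simulation of 2,000,000 normal triples (all correlations are assumptions; the document gives none):

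| Assumed correlation | Chance of at least one false positive |
|---|---|
| 0 | 14.3% |
| 0.3, all pairs | 13.6% |
| 0.5, all pairs | 12.5% |
| 0.8, all pairs | 9.8% |
| 0.9, all pairs | 8.4% |
| 0.8 between the caries measures, 0.2 with oral hygiene | 12.3% |

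The last row is the most realistic pattern: both caries measures come from the same examination and decayed teeth enter both, while oral hygiene is a different construct.

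**3. What each repair does to the sample size**

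*One primary outcome, oral hygiene status:* alpha for the primary claim is 5%, and 212 per group stands.

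*Three primaries with Bonferroni:* alpha = 0.05 / 3 = 0.0167, z = 2.394.

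- Required for oral hygiene: [2.394·0.7065 + 0.8416·0.6934]² / 0.036864 = 140.4, rounded up to 141. Then 141 × 1.5 / 0.9 × 1.2 = 282 per group, 564 in total, against 424.
- Power at the planned effective 106 per group: Φ[(0.192·√106 − 2.394·0.7065) / 0.6934] = Φ(0.41) ≈ 66%, against 80% at alpha 0.05.

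Holm uses the same 0.0167 at its first step, so the loss applies there too unless another measure is rejected first.

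**The case against.** The strongest reply is that the definitions are nested, not rival. Oral hygiene status is one of the three measures, the sample size section names it as primary, and the outcome section defines the Good category. A reader of the whole article can identify the powered endpoint. That is correct, but identifying it does not settle whether a caries result alone would count as primary.

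A second reply is that rules for combining co-primaries, and the exact visit and model, commonly sit in an analysis plan, which may exist. This also stands: the absence of a multiplicity rule in a condensed article is not by itself the fault. The fault is that two sections give different primary outcomes, which a later plan can only resolve by overruling one of them.

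Three stronger readings are tempting and go further than the text allows:

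- *The trial will claim success on any measure.* No success rule is stated. The 5% level for all tests and the aim of informing on each outcome separately leave this open, but do not say it.
- *There are four primary tests, because OHI-S is taken at 6 and 12 months.* That would give 1 − 0.95⁴ = 18.5% if independent. But the analysis section can be read as one longitudinal comparison, so separate tests by visit are not established.
- *The sample size is miscalculated for this reason.* It is not; it reproduces, and simply covers one measure of three.

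**Conclusion.** The contradiction is in the text and needs correcting. The sample size section makes oral hygiene status the sole primary outcome. The outcome section adds two caries measures at the same level, and the secondary list does not take them back.

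The size is conditional. If any one of the three could carry the primary claim, the false-positive rate would be about 10% to 14% instead of 5%: 14.3% under independence, which is an upper-end case, and about 12% if the caries measures are strongly correlated. This assumes two-sided tests, each valid at its nominal level, and correlations of up to 0.8. It illustrates what the wording leaves open and is not an estimate of this trial's error rate. The power figures take the plan's design effect and loss allowances as given.

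**What to change.** Reword the section on primary outcome variables to agree with the sample size section. Name one primary outcome: the proportion with Good status on OHI-S, test versus control, at one visit named in advance. Twelve months is an example; the article ties its two proportions to no visit, so the choice is the sponsor's. Move caries experience, current caries status and OHI-S at the other visit to the secondary outcomes, and say that no claim of effectiveness rests on them alone.

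Cost: no change to data collection, and 424 participants stands on the plan's own arithmetic. Caries results become supportive only. The registry entry, not seen here, should be checked for consistency with the reworded outcome.

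If the sponsor prefers to keep three primaries, the plan must state how they combine. With Bonferroni or Holm, the stated power must be revised to about 66% for oral hygiene at alpha 0.0167, or the sample raised to 564 on the Bonferroni calculation above. Caries assumptions would also have to be supplied, since none are given. That option is more than a wording change.

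### Oral hygiene is scored numerically but defined only in bands and powered as Good versus not Good; a baseline-adjusted score analysis would recover useful power at almost no cost

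*Protocol article*

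**What the plan says.** - **Primary outcome variables:** OHI-S has a maximum of six. The text then states: "Based on their score, each participant will be assigned these three categories". The bands are Good (0.0-1.2), Fair (1.3-3.0) and Poor (3.1-6.0). Group means are specified for DMFT/dmft, but no mean or change is specified for OHI-S.
- **Sample size determination:** "The primary outcome is oral hygiene status", and "The sample size for this study was determined using the formula for comparing two proportions". The planning value is "The prevalence (P_1_ = 38.4%) of children who had good oral hygiene from a previous study in Nigeria", against 57.6% after the intervention. The stated total is 212 per group, with a design effect of 1.5.
- **Baseline and Post-intervention data collection:** OHI-S is examined at baseline, 6 and 12 months, but not at the immediate visit.
- **Data analysis plan:** "Baseline data would be compared among the two study groups", including on the outcome variables. Effects are then to be assessed over time and between groups, with baseline listed as one of the assessments. No scale is fixed for OHI-S, and the Independent variables section does not list its baseline value.

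**The concern.** The examiners already collect a number for each child. Under the stated bands, a child who goes from 3.0 to 1.4 stays Fair and not Good, while a child who goes from 1.3 to 1.2 becomes a success. An analysis of Good versus not Good ignores the first change and counts the second in full.

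Only eight schools are randomised and adding schools is expensive, so it is worth asking how much precision the existing examinations could yield if the score itself, and its baseline value, were used.

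**Working it through.** **Inputs from the protocol article:** 38.4% versus 57.6% Good; 80% power; 5% significance (two-sided assumed); non-response 10%; attrition 20%; design effect 1.5; 212 per group; four schools per arm.

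**Assumptions:** the score is normal with equal spread in both arms. The article gives no SD, distribution or intraclass correlation (ICC).

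**1. The plan's own figure.** With mean proportion 0.48 and 0.384 x 0.616 + 0.576 x 0.424 = 0.4808:

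n = [1.96 x sqrt(2 x 0.48 x 0.52) + 0.842 x sqrt(0.4808)]^2 / 0.192^2 = 105.1, so 106.

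106 x 1.5 = 159, and 159 / 0.9 x 1.2 = 212. The stated 212 reproduces. The article does not show its inflation steps; the simpler variance 2 x 0.48 x 0.52 gives 107, and 107 x 1.5 x 1.1 x 1.2 is also 212.

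**2. The same effect on the score.** d = z(0.576) - z(0.384) = 0.192 + 0.295 = 0.487 SD.

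**3. Child-level cost of the two-way cut.** Relative efficiency is phi(c)^2 / [p(1-p)]:
- p = 0.384: 0.617 (loss 38%)
- p = 0.48: 0.636 (loss 36%)
- p = 0.576: 0.628 (loss 37%)

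In sample-size terms the score needs 2 x 7.849 / 0.487^2 = 66.3, so 67 per arm, against 106 (ratio 0.632). With the unpooled variance the proportion needs 7.849 x 0.4808 / 0.192^2 = 102.4, and the ratio is 66.3 / 102.4 = 0.648.

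Keeping all three ordered bands loses less: about 20-32% for an assumed Poor share of 2-25%.

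**4. Carrying the clustering to the score.** After the planned losses, 212 x 0.9 x 0.8 = 152.6 children per arm, or 38.2 per school. A design effect of 1.5 at that size implies a binary ICC of 0.5 / 37.16 = 0.0135. Dichotomising also dilutes the ICC, so the score's ICC is larger: approximately 0.0135 / 0.636 = 0.0212. The score's design effect is then 1 + 37.16 x 0.0212 = 1.79. The ratio 1.79 / 1.5 = 1.19 turns 0.648 into 0.771 and 0.632 into 0.753, a loss of about 23-25%.

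**5. Power with a t-test on 6 df.**
- Proportion: effective n = 152.6 / 1.5 = 101.8; 0.192 / sqrt(0.4808 / 101.8) = 2.79; power 65%.
- Score: effective n = 152.6 / 1.79 = 85.5; 0.487 / sqrt(2 / 85.5) = 3.18; power 76%.

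**6. Sensitivity to the ICC (38.2 analysed per school, 6 df).**

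| Binary ICC | Score ICC | Design effect, proportion / score | Power, proportion | Power, score |
|---|---|---|---|---|
| 0.0096 (1.5 at 53 per school) | 0.0151 | 1.36 / 1.56 | 69% | 81% |
| 0.0135 (1.5 at 38.2 per school) | 0.0212 | 1.50 / 1.79 | 65% | 76% |
| 0.05 (assumed) | 0.0785 | 2.86 / 3.92 | 40% | 44% |
| 0.10 (assumed) | 0.157 | 4.72 / 6.82 | 27% | 28% |

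**7. Baseline adjustment.** An assumed baseline to follow-up correlation r multiplies the child-level variance by 1 - r^2: 0.91, 0.75 and 0.51 for r = 0.3, 0.5 and 0.7. At r = 0.5, with only the within-school part reduced, the variance in row two of the table is (2/4) x (0.0212 + 0.9788 x 0.75 / 38.16) = 0.0202. Then 0.487 / sqrt(0.0202) = 3.42, and power is about 81%. Adjustment would help the proportion as well.

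**The case against.** **The score may still be analysed.** Assigning a band does not mean dropping the score, and a trial powered on a proportion may still compare means. The Data analysis plan names no scale or model, and those details commonly sit in a statistical analysis plan that is not shown. This stands. A reader might infer that the trial will throw the score away; the article does not say so. The loss is certain only for the sample-size basis and conditional for the analysis. What the article does fix is the definition of the outcome in bands and the power basis.

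**More than a third lost?** A reader might take the 36-38% as the trial's loss. It belongs to a two-way cut of a normal score at child level. The outcome definition sets three bands, which lose less, and a logistic-shaped score would lose about 18-22% under the two-way cut.

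**Do the eight schools make it worse?** A reader might think so, or might apply the design effect of 1.5 unchanged to the score and obtain 82% power. Neither holds. The score carries a larger design effect, and where between-school variation dominates, changing the scale recovers little. Nor do the documents show that this is the largest gain available, since no alternative can be costed from them.

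**The bands are established.** They come from the cited index, and the planning prevalence exists on that scale. This is a good reason to keep reporting the proportion Good, but not a reason to leave the score unused.

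**Conclusion.** The point holds as an improvement in the choice of analysis; it is not an error in the sample size, which reproduces. If oral hygiene is analysed as Good versus not Good, the cut costs about 36-38% of the information at child level and about 23-25% after clustering at the stated design effect. On 6 df that is about 65% power against 76%, before baseline adjustment.

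These figures rest on a normal score with equal spread, the planned losses occurring in full, and the stated design effect being right. Skewness would change them. If the ICC is 0.05 or more, the gain falls to a few percentage points and the choice of scale matters little beside the number of schools.

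**What to change.** Pre-specify the between-arm difference in mean OHI-S at a named follow-up examination, adjusted for the child's baseline OHI-S and accounting for school as the unit of randomisation. Make it the primary analysis, or at least a key supporting one. Adjust the Good versus not Good comparison for baseline OHI-S too, and report the proportion Good with its confidence interval alongside.

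The cost is a few sentences and one more model, with no extra fieldwork. The drawback is that a mean difference in OHI-S is less familiar to policy readers than a percentage Good, which is why both should be shown. If both are kept, the text must say which one is primary.

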#### Secondary outcome variables

The secondary outcome variables include participants’ oral hygiene knowledge, attitude, and practices. There will be six questions assessing the participants’ knowledge. Each correct answer will be awarded a score of “1” and the wrong option “0”. Each participant’s knowledge score will be compiled over six. Similarly, there will be five questions to assess their attitude. The options will be a Likert scale (strongly disagree to strongly agree). The best response, which indicates the most positive attitude to the statement on oral hygiene, will be given the highest score of “5” while the most negative response will be scored “1”. The total attitude score for all the participants will be computed with the maximum being “25” and the minimum being “5”. The participants’ oral hygiene practices that would be assessed include twice daily brushing, the presence of fluoride, and the size of dispensed toothpaste for brushing. Others are their technique of tooth brushing and how long before they changed their toothbrush.

#### Independent variables

The independent variables would include the participants’ study group, sociodemographic characteristics (age, gender, neighbourhood), and school-related characteristics (school type, class level).

### Validity and reliability of the questionnaire

The questionnaire (Appendix I) contains mainly structured questions, with a few carefully selected open-ended questions to ensure valid responses. The questionnaire contained questions that will be easy to administer, and the importance of giving steady answers by the respondents will be emphasised. The questionnaire was face- and content-validated by dental public health experts, and they considered the questions adequate to answer the research questions and appropriate for the intended age group. The data collectors will be trained on the mode of administering the questionnaires to avoid interviewer bias. The questionnaires will be pretested among a minimum of 20 pupils in communities outside Igboora and Idere with similar relevant characteristics to the study population. The students will be asked to give feedback on the clarity of the questions and other useful information will be used to improve the questionnaire. The pretest will be done to assess the reliability of the questions, including the knowledge and attitude scales and their responses will be analysed using the test statistics of Cronbach’s reliability test. The five examiners will also individually provide oral examinations for all 20 pupils. The examiners’ agreement on the recorded scores for the simplified oral hygiene index and dmft/DMFT will be evaluated using the Cohen Kappa statistics.

### Data management plan

#### Data handling plan

The questionnaires will be checked for errors daily, and necessary corrections will be made as soon as they are discovered. Each response on the questionnaire will then be coded and recoded on a coding sheet. The codes for each response on the questionnaire will then be entered into Statistical Package for Social Science (SPSS) Version 25, after which the coded data will be checked for errors by cross-checking 10% of the data.

#### Data analysis plan

Baseline data would be compared among the two study groups based on their sociodemographic characteristics and the baseline value of the outcome variables (oral hygiene status, DMFT/dmft, caries status, knowledge, attitude, and practice). Subsequently, the intervention effects on the outcome variables will be assessed over the study period (baseline, immediate, 6 months, and 12 months assessments). The effectiveness would also be compared between groups (test vs control) over the 12 months (baseline, 6 months, and 12-month assessment). An intention-to-treat analysis will be employed for this study [51]. A participant will remain in the originally assigned group, notwithstanding what happens during the study, such as deviation from the study protocol or loss to follow-up. The data obtained at the previous assessment will be recorded for those lost to follow up in the subsequent assessments. The level of statistical significance for all tests will be set at p < 0.05.

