The participants in the control group will be exposed to conventional health education on adequate oral hygiene practices conducted by the dentist [50]. Similar to the test group, there will be three intervention sessions. The first session will last for 40 minutes and will involve expert-led health talks and question and answer with the participants. The second and third sessions will also take place after two and four weeks, respectively. The follow-up sessions will involve revising the oral health messages with the participants, lasting for about 20 minutes each. None of the participants (control and test groups) will be denied access to oral health talks that they may be exposed to away from school.

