### Post-intervention data collection

There will be three sessions of post-intervention assessments—Immediate, six, and 12 months. The immediate post-intervention assessment will collect information on the participants’ oral hygiene knowledge and attitude immediately after the second session of the intervention is completed. The 6-month post-intervention assessment will be conducted six months after the immediate post-intervention assessment. Information on the participants’ oral hygiene knowledge, attitude, and practices will be collected. Oral examinations will also be done to assess the participants’ oral hygiene status using the simplified oral hygiene index. The 12-month post-intervention assessment will be conducted 12 months after the immediate post-intervention assessment. It will involve oral health examinations to check the participants’ oral hygiene status and dental caries experience (dmft/DMFT), along with assessing the participants’ oral hygiene knowledge, attitude, and practices. The same questionnaire for the pre-intervention assessment will also be used for the post-intervention assessments. However, the immediate post-intervention assessment will not include oral examinations. The questionnaires for 6 and 12 months post-intervention data collection will include a question to assess if the participants have been taught oral hygiene practices (through songs or lectures) by pupils from other schools during the study period. This is to get data on the potential contamination and control for this during the data analysis (sub-analysis).

Figs 2 and 3 show the SPIRIT schedule and Flow diagram for the study, respectively.

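### The test-versus-control comparison omits the immediate assessment, so knowledge and attitude have no stated randomised contrast at that time point

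*Protocol article*

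**What the plan says.** The Data analysis plan describes the post-baseline analysis in two consecutive sentences. The first says that "the intervention effects on the outcome variables will be assessed over the study period (baseline, immediate, 6 months, and 12 months assessments". It names no comparator. The second adds: "The effectiveness would also be compared between groups (test vs control) over the 12 months (baseline, 6 months, and 12-month assessment". This is the only post-baseline analysis in the article that is labelled as a comparison of the arms.

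Under Post-intervention data collection, the immediate assessment covers "oral hygiene knowledge and attitude immediately after the second session of the intervention is completed". The same section states that "the immediate post-intervention assessment will not include oral examinations", and that the baseline questionnaire is used again afterwards. Practices and oral hygiene status are added at 6 months, and caries experience at 12 months.

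Under Secondary outcome variables: "The secondary outcome variables include participants’ oral hygiene knowledge, attitude, and practices". Knowledge is scored out of 6 and attitude from 5 to 25.

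For the control arm, Intervention and control groups says: "Similar to the test group, there will be three intervention sessions". These sessions run to the same timetable as in the song arm. The first is a 40-minute expert-led talk with questions, and the later ones revise the messages.

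**The concern.** The two sentences give different visit lists, and the visit that drops out of the between-arm list is the one at which only knowledge and attitude are due to be measured. Followed as written, the plan would report intervention effects at the immediate assessment without stating that they are differences between randomised arms.

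This matters because before-after change in the song arm does not isolate the song. The control children are also being taught, by a dentist, on the same schedule, so both arms should gain. The same questions are put to the same children after a short interval, so some gain from repetition is plausible in both arms. Only a concurrent comparison of the arms removes these shared components.

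Knowledge and motivation, which includes attitudes, are two of the three determinants in the behavioural model that the article adopts as its framework. A short-term effect on them is something the authors can be expected to report and interpret.

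**Working it through.** No figure in the plan is in dispute. The check sets the visit lists against the outcomes collected.

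**Visit lists (Data analysis plan)**

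| Assessment | Intervention effects over time (no comparator named) | Test versus control |
|---|---|---|
| Baseline | listed | listed |
| Immediate | listed | not listed |
| 6 months | listed | listed |
| 12 months | listed | listed |

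**Outcomes assigned to each post-intervention assessment (Post-intervention data collection)**

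| Outcome | Immediate | 6 months | 12 months |
|---|---|---|---|
| Knowledge, attitude | yes | yes | yes |
| Practices | not assigned | yes | yes |
| Oral hygiene status | no examination | yes | yes |
| Caries experience | no examination | no | yes |

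Together, the tables show that the omission costs nothing for oral hygiene status, caries or practices, which are not due at the immediate assessment. It leaves knowledge and attitude at that one visit without a stated between-arm contrast.

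**Is the contrast feasible?** The abstract describes assessment of the participants at all four times. The data collection section does not restrict the immediate assessment to one arm, and the two arms share a session timetable. Data from both arms is a fair reading, although the section does not name both groups for this visit as Baseline data collection does for baseline.

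**Interval between questionnaires.** Baseline is one week before delivery starts. The second session is two weeks after the first, and the immediate assessment follows it. So 1 + 2 = about 3 weeks.

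**What before-after change measures.** Let g be the gain that both arms share (content common to song and talk, repeat questioning, other events in the schools), and d the difference between song and talk. Then:

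- change in song arm = g + d
- change in control arm = g
- randomised contrast = (g + d) − g = d

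The before-after figure exceeds the randomised one by g, whatever d is. The documents give no value for either. As an assumed illustration on the six-item knowledge score, gains of 1.2 with the song and 1.0 with the talk give a before-after figure of 1.2 and a randomised contrast of 1.2 − 1.0 = 0.2. If g were 0, the two figures would agree.

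**Number of children.** The 424 is a recruitment minimum that already includes allowances for 10% non-response and 20% attrition. Applying both gives 424 × 0.9 × 0.8 = 305. Since the timing of losses is not stated, the number assessed at this visit could lie anywhere between about 305 and 424.

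**Sample size.** The stated 212 per group is for oral hygiene status and has no bearing on this point. It reproduces closely with the unpooled two-proportion formula (two-sided 5% assumed, 80% power): (1.96 + 0.842)² × (0.384 × 0.616 + 0.576 × 0.424) / 0.192² = 102.4; × 1.5 = 153.5; / (0.9 × 0.8) = 213.

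**The case against.** The strongest reply is that the plan nowhere says before-after or within-group. In a two-arm trial, intervention effects over several visits could mean a group-by-time comparison, and study group is listed among the independent variables without limit to particular visits. This stands in part: a reader might infer that the authors have committed to an uncontrolled analysis, and the text does not go that far. But the second sentence is introduced as an additional analysis and carries its own between-group label, so the natural reading is that the first is something else. If both were meant to compare the arms, the two lists disagree and need reconciling anyway.

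A second reply is that the immediate assessment was left out because it has no oral examination. That explains the omission for oral hygiene and caries, but not for knowledge and attitude. Nor is the between-group sentence confined to examination outcomes. If it were, these two scores would have no named between-arm comparison at 6 or 12 months either.

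A third reply is that this is detail for a full analysis plan that is not shown. Models and tests can fairly be left there. Here, however, the article itself fixes a visit list and leaves one assessment off it.

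Three stronger readings are not supported:

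- **The arms should differ most at this visit.** The documents do not say so. The assessment follows the second of three sessions, with daily singing still under way, and the case made for songs includes retention and lasting habits.
- **The immediate scores enter no randomised comparison at all.** The plan carries the previous assessment forward for children lost to follow-up, so some immediate scores can stand in for 6-month values in the between-arm comparison. They are still not compared at their own time point.
- **The trial's conclusions on effectiveness are compromised.** Knowledge and attitude remain under a controlled comparison at 6 and 12 months.

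**Conclusion.** The point holds in a limited form. The between-arm list omits the immediate assessment, and no other part of the article supplies a test-versus-control contrast there. Knowledge and attitude, as secondary outcomes, therefore lack a stated randomised comparison at that visit, and an effect reported for it could include gains common to both arms.

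The size is two secondary outcomes at one of three post-intervention assessments. The primary outcome, the later comparisons and the sample size are untouched. The amount by which a before-after figure would mislead cannot be derived from the documents.

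The conclusion rests on two readings: that the sentence naming no comparator is not itself a between-arm analysis, and that both arms are assessed at the immediate visit. It is worth correcting before analysis because the remedy needs no new data, but it does not threaten the trial's main result.

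**What to change.** Replace the between-group sentence for these outcomes with wording such as: knowledge and attitude scores will be compared between the test and control groups at the immediate, 6-month and 12-month assessments, adjusted for the baseline score and allowing for clustering by school. Keep the existing visit list for practices, and for oral hygiene status and caries at the visits where each is measured. State that changes within an arm are descriptive and are not estimates of the intervention effect. Confirm in the data collection section that the immediate assessment is made in both arms.

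The cost is a few lines of wording. On the fair reading that both arms are assessed at this visit, no extra visit, data or sample size is needed.
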